### Study setting

All patients will be recruited from the aforementioned outpatient mental health clinic. This clinic roughly facilitates 120 intakes per month at various sites for adult and elderly care in the province of Limburg, which is situated in the South of the Netherlands. The pre-intake for patients being referred to the outpatient mental health clinic will be facilitated by an eHealth organization providing provisional diagnoses for incoming patients. All patients will learn about study 1 or study 2 during the recruitment procedure, as outlined below.

### Recruitment process

The recruitment procedures below will be applicable to both study 1 and study 2, but differences will be described when necessary. Each patient will undergo a pre-intake at the eHealth organization, which is part of the standard intake procedure for patients being referred to the outpatient mental health clinic. During this pre-intake process, patients will be asked to complete several online questionnaires. Subsequently, each patient will receive a 15-minute consultation with a triage psychologist via telephone. This pre-intake procedure will result in an indication of the patient’s symptoms and a potential diagnosis. Based on this care indication, the outpatient mental health clinic will be advised to either start with treatment or to refer back to the general practitioner. In the latter case, the patient’s symptoms are considered too mild for treatment at the mental health clinic, and participation in the studies will therefore not be possible. Total study eligibility will be assessed using the aforementioned criteria for inclusion and exclusion during this pre-intake. If a patient is deemed eligible for study participation, the triage psychologist will ask whether the patient is interested in receiving study information. A flowchart of the RCT is presented in Fig. 1 below, providing a brief overview of the pre-intake by the eHealth organization, the study enrollment via the O4U-system, the randomization procedure, the key constructs measured in Limesurvey at multiple time points, and the anticipated start of treatment at the outpatient mental health clinic.

### eHealth positive psychology intervention (eHealth PPI)

An existing online positive psychology intervention (eHealth PPI), which has been successfully implemented for patients with chronic pain [22], will be adapted for patients with various mental health complaints and their loved ones. The current eHealth PPI consists of 9 modules. This intervention aims to increase five protective factors, including self-compassion, positive focus, savoring, gratitude and optimism, which will be offered during an eight-week period. Each participant will be asked to spend approximately 4 h per week on each module. Module 1 presents an introduction about the eHealth PPI, including information on its applicability. Module 1 and module 2 be accessible at the same time. Both module 2 and 3 target self-compassion, which refers to fully accepting oneself, the ability to treat oneself with kindness rather than self-criticism, and recognizing that everyone experiences failures [53]. Both modules aim to teach patients to become more self-reliant when dealing with the emotional consequences of their condition or stressful events. Higher rates of self-compassion are generally associated with improved psychological and physical well-being [54]. Module 4 requires patients to practice the ‘three good things’ exercise on a daily basis [55]. In this module, patients write down three good things that happened that day and why they happened. This exercise aims to shift the focus from a negative orientation towards a more positive one, by raising awareness for the good things in life [56]. Module 5 and 6 are about savoring, which is the capacity to attend, appreciate and enhance the positive experiences in life [57]. From a psychological perspective, savoring is considered a meaningful resource for coping with adversity and amplifying subjective well-being [58]. These modules contain savoring techniques promoting the frequency and intensity of positive experiences in daily life. Module 7 is about gratitude, which represents the ability to identify and acknowledge the valuable things in life [59]. Practicing gratitude frequently may increase well-being [60]. Module 8 contains the Best Possible Self exercise [61], which is aimed at increasing optimism: the tendency to have constructive and positive future expectancies [62]. Optimism has been associated with beneficial coping strategies, applying different coping strategies more flexibly, increased subjective well-being, longevity, and decreased illness [63]. Finally, module 9 aims to prevent relapse, using a personalized maintenance plan. Developing a personalized maintenance plan for positive psychology exercises may encourage future application of the learned methods [64]. During the eHealth PPI, a psychologist from the Open University will organize weekly contact moments (via e-mail) to offer support, to enhance adherence, and to prevent drop-out.

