#### Measuring societal costs for the CEA and CUA

In both the CEA and CUA, costs will be measured among patients from a societal perspective, including healthcare costs (i.e., health services use and medications), productivity losses (i.e., absenteeism and presenteeism), and intervention costs (i.e., the costs of implementing the intervention). To measure healthcare costs and productivity losses, a 3-month recall period will be used. Consumption of health services, medications, and productivity losses in patients facing psychological complaints will be measured, using the Treatment Inventory of Costs in Patients with psychiatric disorders (TIC-P) [87].

By definition, the TIC-P was developed as a generic questionnaire to estimate societal costs across all Dutch adult mental health populations within inpatient and outpatient clinical settings. Using both categorical multiple choice and numerical open ended questions, the TIC-P aims to measure 3 subscales: general demographics (7 items), healthcare consumption (38 items), and productivity losses in both the formal and informal workspace (12 items) [87]. In the absence of subscale estimates (e.g., Cronbach’s alpha) on reliability, Cohen’s Kappa was still considered highly satisfactory for most separate items on healthcare consumption, and satisfactory for most items on productivity losses [88]. Productivity losses in the workspace are based on absenteeism (i.e., not being able to work) and presenteeism (i.e., reduced productivity in the workspace). Informal productivity losses related to unpaid work will also be measured. Patients will report their hours of absence (i.e., absenteeism) and the additional hours they needed to finish work due to health complaints (i.e., presenteeism).

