In addition, intervention costs related to the implementation of the eHealth PPI will be prospectively recorded during the trial using a Microsoft Excel sheet. Following the recent guidelines for economic evaluation issued by Zorginstituut Nederland (ZIN) [65], the measured intervention cost categories are: [1] personnel time, [2] training costs, [3] licensing and platform maintenance, [4] development costs, and [5] technical support. If possible, annual invoices from the participating eHealth organization will be used to assess relevant eHealth PPI implementation costs. More specifically, [1] personnel time includes the amount of time spent by healthcare staff to supervise participants during the eHealth PPI (e.g., providing feedback and responding to alerts). This time investment is a variable cost component and will be derived using digital logs on the eHealth platform and self-reported tracking by staff members from the eHealth organization and Open University. If applicable, [2] additional training costs related to good supervision practices among staff members will be documented as fixed costs, including required resources and preparation time. Annual fees related to [3] licensing and platform maintenance will be retrieved from invoices provided by the eHealth organization. If not covered by licensing fees, additional [4] development costs related to the eHealth software will be recorded and treated as fixed costs, based on provider documentation from the eHealth organization. If [5] technical support costs for participants (e.g., IT helpdesk support) are invoiced separately from licensing and service agreements, the frequency and variable costs per user will be measured using these invoices. Lastly, all healthcare, non-healthcare and intervention cost components will eventually be valued, using the most recent costing manual in Dutch healthcare [66].

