##### Login frequency data

To further explore the accessibility of the eHealth PPI, differences in PPI starting time among participants (i.e., the time between providing informed consent and starting the first PPI module) will be measured in both studies using login frequency data from the eHealth platform. Adherence, defined as the extent to which study participants comply with the basic eHealth PPI protocols (i.e., moving through all required tabs within a module and finishing digital homework assignments), will also be measured in both studies using login frequency data. Lastly, the same login frequency data aims to measure engagement in both studies, defined as the depth of interaction between study participants and the modules of the eHealth PPI. In this context, engagement is measured by assessing both the total time spent on each PPI module and the interactions between study participants and the optional drop-down menus within each PPI module, including additional information and homework assignments.

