Apart from the anticipated strengths, certain operational challenges in performing the studies need to be addressed. Firstly, not all patients are equally knowledgeable about eHealth, neither are they equally literate. In fact, intervention adherence among participants may be compromised due to low eHealth literacy [111]. To address this challenge, an evaluation of implementation procedures will be conducted to examine and optimize the eHealth PPI from a user-perspective, using a variety of quantitative and qualitative approaches prior to and during both studies. Secondly, dropout among patients and loved ones may be related to the weekly 4-hour time investments required to complete an intervention module, the extensive measurements and confrontational questionnaires [112]. To mitigate this risk, precautionary measures will be taken to ensure that the time spent on each measurement will be at most 30 min. These measures include using brief, yet validated questionnaires addressing the research objectives. Thirdly, the two eHealth PPI arms (with and without loved ones) will be compared to each other exploratively in study 2, since there is no information about effect sizes available to perform a fully powered analysis. Until all data are collected, it remains unclear whether the sample size of study 2 is adequate for this purpose. In fact, the expected difference in effects between both PPI arms is likely smaller than the difference between each PPI arm and the TAU arm, which was considered the foundation for the a priori sample size calculation. If this turns out to be the case, the statistical power may fall below the conventional 80% threshold and true differences may remain undetected. In that case, any conclusions about the generalizability of upcoming findings should be drawn with greater caution. That being said, the interim analyses aim to estimate the actual effect size, which is informative for both PPI forms (with and without loved ones) in our research setting. More specifically, this estimation of the actual effect size may guide future research initiatives aimed at developing a confirmative study design employing both PPI forms with a sufficient degree of statistical power, without compromising the most important contrasts (i.e., PPI for patients vs. TAU and PPI for patients + loved ones vs. TAU). Fourthly, assessing (cost-)effectiveness may be complicated due to the heterogeneity of the target populations addressed in the current project. Apart from loved ones, various clinical patient populations are eligible for participation. Since clinical factors may substantially affect costs and treatment outcomes, certain clinical profiles (i.e., severity of psychological complaints, and diagnosis) will be included as covariates in both studies. Fifthly, the proposed recruitment procedures at the Dutch mental health clinic and the eHealth organization are aimed at minimizing selection bias, which may optimize the representativeness of vulnerable patient populations in our studies. However, a selectively induced bias among participants may not be ruled out entirely, since vulnerable target groups (e.g., individuals with low literacy) are less likely to seek psychological treatment and to participate in digital research [113, 114]. Lastly, the southern regions in the Dutch province of Limburg are characterized by significant socio-economic challenges [113], which could affect the broader generalizability of upcoming study findings on a national level in The Netherlands.

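### Participants' own time on the PPI, about 32 h requested per person, is priced nowhere in the societal cost; a symmetric scenario analysis should show whether the ICERs withstand it

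*Protocol article*

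**What the plan says.** On the burden, the section *eHealth positive psychology intervention (eHealth PPI)* states: "Each participant will be asked to spend approximately 4 h per week on each module". It also says "The current eHealth PPI consists of 9 modules" and, of the programme, "which will be offered during an eight-week period". The Discussion repeats the burden as "weekly 4-hour time investments required to complete an intervention module" and names it as a possible reason for dropout.

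On costs, *Measuring societal costs for the CEA and CUA* says that "costs will be measured among patients from a societal perspective". It defines three components: use of care and medication, lost productivity (absenteeism and presenteeism), and the cost of implementing the intervention. For the last of these, "the measured intervention cost categories are: [1] personnel time, [2] training costs, [3] licensing and platform maintenance, [4] development costs, and [5] technical support". Personnel time is defined there as the time of supervising staff. The same section adds: "Informal productivity losses related to unpaid work will also be measured". *Valuation of societal costs* then sums the three components into the societal cost per arm.

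On data, *Login frequency data* says that "engagement is measured by assessing both the total time spent on each PPI module" and the use of optional drop-down menus. The hours are therefore recorded, but for the process evaluation and not for costing.

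**The concern.** The intervention is largely self-guided, with weekly e-mail support, so much of the effort falls on participants. The plan counts the provider's inputs in detail and leaves out the participants' hours. Those hours are requested in arms 1 and 2 and are zero by design in TAU. In arm 2 they are requested twice, once from the patient and once from the loved one.

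What is at stake is the cost difference in the two main economic contrasts (arm 1 vs TAU and arm 2 vs TAU) and in the comparison of arm 2 with arm 1. A cost that falls only on the PPI side and is left out will tend to make the ICERs and the acceptability curves look better for the PPI, unless the PPI saves participants a comparable amount of time elsewhere.

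**Working it through.** **Is the time captured under another cost line?** Setting the sections side by side:

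- Intervention costs: all five items are on the provider side. Personnel time is staff time.
- Productivity losses: presenteeism is the extra hours that patients needed to finish work because of health complaints, not hours spent on modules.
- Unpaid work: the TIC-P measures losses here, but *Valuation of societal costs* describes a valuation only for absenteeism and presenteeism. Time given to modules is also not necessarily unpaid work lost.
- Loved ones: Table 2 gives the TIC-P to patients only. *Valuation of societal costs* recognises the loved one's user account as an added intervention cost, but not the loved one's hours.
- Sensitivity analyses: *Cost-effectiveness: base-case analyses* varies parameters of costs and health service use. Varying listed items does not bring in an unlisted one.

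Participants' PPI time is therefore in none of the components.

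**Hours.** The article gives no total, so there is no stated figure to reproduce.

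- 4 h per week x 8 weeks = 32 h per participant.
- Variant by module: 4 h x 9 modules = 36 h. Module 1 is an introduction opened together with module 2, so 32 h is the more natural reading.
- Half adherence: 0.5 x 32 = 16 h.
- Arm 2 pair: 2 x 32 = 64 h.

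**Value.** Assumption: EUR 10-20 per hour, because the documents give no hourly price. Cost = hours x price. QALY equivalent = cost / EUR 20,000, the threshold that the article adopts.

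| Case | Hours | Cost (EUR) | QALY at EUR 20,000 |
|---|---|---|---|
| One participant, full adherence | 32 | 320-640 | 0.016-0.032 |
| One participant, 50% adherence | 16 | 160-320 | 0.008-0.016 |
| Patient and loved one, full adherence | 64 | 640-1,280 | 0.032-0.064 |

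With a wider assumed price of EUR 5-40 per hour, 32 h is EUR 160-1,280, or 0.008-0.064 QALY.

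**Direction.** Let D be the hours by which patients in a PPI arm spend less time in other care than TAU patients. The net omitted time against TAU is then 32 - D hours per patient at full adherence, or 16 - D at half adherence. The omission favours the PPI as long as D is below that figure, and the sign turns only if D exceeds it. The documents give no value for D. In arm 2 vs arm 1, patient PPI hours cancel if adherence is equal, and the loved one's hours, up to 32, remain.

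**The case against.** The strongest case against has four parts.

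First, no rule in the documents requires this time to be priced. The costing follows national guidelines and a costing manual that are cited but not shown. A reader might infer that the plan breaks the societal perspective it claims, or that the base case is wrong. The documents do not support that, because they contain no standard against which to call the exclusion an error.

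Second, the sign is not certain. PPI time is zero in TAU, but patient time is not. The Background says that patients may receive GP-MHP care or use other resources while waiting. The PPI is offered as an alternative to GP-MHP care, and the Discussion hopes for fewer treatment sessions later. Patient time in all that care is unpriced in every arm. Pricing PPI time alone, with nothing for other care, would be lopsided in the opposite direction.

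Third, the hours are soft. Thirty-two is what is requested, not what will be spent. Several exercises, such as the daily listing of good things and savoring, are done away from the screen, so platform logs may miss them. Such practice may also displace leisure, whose price is a methodological choice. The plan's counting of lost unpaid work does not make its silence on module time an inconsistency.

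Fourth, an article condenses a fuller document. This point carries least weight, since the article itself numbers the intervention cost lines and states the sum that they enter.

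The first three points stand. They limit the size and certainty of the effect and they shape the remedy. They do not alter the fact that a cost requested only in the PPI arms is absent from the stated cost definition.

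**Conclusion.** The point holds as a cheap improvement, not as the correction of a wrong statement. The societal cost as defined leaves out about 32 h of requested participant time, for patients in arms 1 and 2 and for loved ones in arm 2. This probably lowers the incremental cost of both PPI arms against TAU, and of arm 2 against arm 1.

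The amount is EUR 320-640 per participant, half that at 50% adherence, and up to double per pair in arm 2. The QALY gain needed to cover it for one participant is 0.016-0.032 at EUR 20,000 per QALY. These figures rest on the assumed EUR 10-20 per hour and, except where halved, on full adherence. They are gross of any time that the PPI saves in other care. It would go too far to say that the ICERs are certainly biased in the PPI's favour by this amount, because offsetting time is unpriced in all arms and unknown.

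**What to change.** Keep the base case. Add one scenario to the sensitivity analyses announced in *Cost-effectiveness: base-case analyses*:

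1. Value participants' PPI time for patients in arms 1 and 2 and for loved ones in arm 2. Use the module time logged on the platform as the lower bound and the requested 4 h per week as the upper bound.
2. Take the price per unpaid hour from the costing manual already in use, or state a range if it gives none. State the assumption that module hours fall outside paid work, since the TIC-P as described does not separate them from absence.
3. In the same scenario, value patients' time for the care contacts reported in the TIC-P in all three arms, with a stated assumed time per contact, so that the comparison is symmetric.
4. Report ICERs and CEACs with and without the scenario for arm 1 vs TAU, arm 2 vs TAU and arm 2 vs arm 1.

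The cost is one extra scenario and a few stated assumptions. It uses login and TIC-P data that are already planned, so no new measurement is needed. The downside is that the PPI may look somewhat less favourable under it.

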
#### Specific design adjustments

The proposed eHealth PPI will address differences in digital skills, low literacy and limited proficiency in the Dutch language within the design of the eHealth PPI. These barriers will be addressed in the eHealth PPI by making the following adjustments: creating short texts, avoiding diagnosis-specific terms, adding or removing theories, optimizing the readability in accordance with Dutch guidelines for addressing low literacy, using persuasive techniques (i.e., newly developed videos, animations, visual content and spoken texts) to optimize engagement, visual attractiveness and attention span. To avoid overwhelming users, explanatory texts and assignments will be positioned in a drop-down menu for users desiring in-depth information about a module.

## Data collection

Implementation procedures of the eHealth PPI will be assessed from a user-perspective in study 1, focusing on: acceptability, feasibility, engagement, adherence, and accessibility. In study 2, outcome variables for assessing clinical effectiveness and procedural implementation will be collected. In addition, study 2 will employ a cost-effectiveness analysis (CEA) and cost-utility analysis (CUA) of the eHealth PPI from a societal perspective, following the recent guidelines issued by Zorginstituut Nederland (ZIN) [65, 66]. In the CEA, the costs and clinical effects of the two eHealth PPI conditions (arm 1 and arm 2) will be weighed against those of the TAU condition (arm 3). Within the CEA, the primary clinical outcome to be collected is a measure for positive mental health. Similarly, in the CUA, the costs and utility outcomes of the two eHealth PPI conditions (arm 1 and arm 2) will be evaluated against those of the TAU condition (arm 3). Within the CUA, the primary outcome to be collected is quality-adjusted life years (QALYs).

